### Outcome measures

Outcomes variables are measured at baseline, 6 months, and 12 months, to both participants and peer leaders. The primary expected outcome is the change in HbA1c at baseline compared to the sixth month and baseline to the twelfth month. HbA1c, a measurement of glycosylated haemoglobin, is regarded as the gold standard measure of glycemic control reflecting overall blood glucose values over the previous 8–12 weeks [30, 31]. There is a strong relationship between HbA1c and the risk of developing long-term diabetic complications and it is accepted as a reasonable surrogate for long-term outcomes in individuals with diabetes. Secondary outcomes are advanced glycation end products (AGEs) [32, 33], blood pressure, BMI, blood lipids, blood glucose (fasting plasma glucose and 2 hour post load glucose), patient-reported rates of severe hypoglycaemia, diabetes self-care activities, medication adherence, knowledge, quality of life, diabetes self-efficacy, traits, life satisfaction, depression, anxiety, and stress. In addition, cost is also assessed.

### Data analysis

Social demographic data and health status of the study subjects are presented as frequencies (percentage) for categorical variables, and means ± standard deviations for continuous variables. Comparison of patients characteristics between groups will be checked by means of T-tests or χ^2^ tests, or non-parametric equivalents. Repeated measures analysis of variance and multilevel analysis for longitudinal data will be used to examine longitudinal differences between groups on primary and secondary outcome measures. Evaluation of intervention effectiveness will be by intention to treat using the above statistical tests. Evidence of clustering by clinic site and primary care provider will be examined and adjusted for analyses as needed. If significant differences in baseline characteristics are found, analyses will be repeated adjusting for these differences using ANOVA and logistic regression for multivariate analyses. Analysis of covariance (i.e. linear regression models for 12-month measurements with baseline scores and intervention arm as covariates) will estimate the changes from baseline to 12 months that can be attributed to the peer support intervention. Sensitivity analyses will be performed to estimate the effects of missing data using different assumptions (e.g. imputed values).The EuroQoL 5 dimensional health state measure (EQ5D) score at base-line and follow-up can be converted into utility weights using the EQ5D algorithm [34], which then allow for the calculation of quality adjusted life years(QALYs). Economic analyses will be employed to estimate direct and indirect cost analysis, the cost per QALY gained and incremental cost-effectiveness ratios. Sensitivity analysis will be undertaken to test the stability of the analysis in terms of the cost inputs and health outcomes. All analyses will be carried out with SPSS 10.0 software.

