### Sample size calculation

Sample size and power calculations are performed for the main outcome of interest-difference in mean HbA1c levels-using effect sizes and standard deviations derived from multiple published trials of patient-education interventions. Using a non-inferiority design based on clinically relevant difference of HbA1c of 0.5%, standard deviation of 1.5, and groups of 8–15 participants per randomisation group for 80% power at two-sided 5% significance, 150 participants are required to complete the study procedures. Allowing for a 20% drop-out from randomisation to completion of the trial, it is anticipated that we would require 180 subjects in each arm to be randomised in the study.

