### Data collection and outcome measures

Data will be collected at baseline, 6 months and 12 months for both intervention groups and comparison group. Table 1 shows the measurement tools of data collection, the method of data collection and the time points of data collection.

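### Two of the three methods named for HbA1c, repeated measures ANOVA (under the intention-to-treat label) and the 12-month ANCOVA, are complete-case as written; only the multilevel model keeps patients with partial follow-up

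*Protocol article*

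**What the plan says.** All places are in the protocol article.

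- **Outcome measures:** "The primary expected outcome is the change in HbA1c at baseline compared to the sixth month and baseline to the twelfth month".
- **Data collection and outcome measures:** "Data will be collected at baseline, 6 months and 12 months for both intervention groups and comparison group".
- **Data analysis, longitudinal comparison:** "Repeated measures analysis of variance and multilevel analysis for longitudinal data will be used to examine longitudinal differences between groups on primary and secondary outcome".
- **Data analysis, next sentence:** "Evaluation of intervention effectiveness will be by intention to treat using the above statistical tests".
- **Data analysis, later:** an ANCOVA, described as "linear regression models for 12-month measurements with baseline scores and intervention arm as covariates", is to estimate the change to 12 months attributable to peer support.
- **Data analysis, missing data:** "Sensitivity analyses will be performed to estimate the effects of missing data using different assumptions (e.g. imputed values", in parentheses).
- **Sample size calculation:** "Allowing for a 20% drop-out from randomisation to completion of the trial", the plan randomises 180 per arm so that 150 complete.

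No sentence says which of the three methods gives the main HbA1c result.

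**The concern.** Intention to treat means that randomised patients are analysed in their allocated arm, as far as their data allow. Standard repeated measures ANOVA removes any patient who lacks one of the three HbA1c values. The ANCOVA, as described, removes any patient without a 12-month value and has no place for the month-6 value. Unless values are imputed, both analyse completers, and the plan mentions imputation only under sensitivity analyses.

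One of these methods falls under the intention-to-treat sentence. The other supplies the effect attributed to the intervention. A patient seen at month 6 and then lost has a measured response that neither uses. If such patients differ between the arms, for instance because poor responders leave one arm more readily, the 12-month comparison of those who remain is distorted. The multilevel model can use the month-6 value and so corrects for loss that depends on observed HbA1c.

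**Working it through.** **1. The plan's own figures.** From the sample size section: difference 0.5, SD 1.5, 80% power, two-sided 5%, 150 completers, 20% drop-out, 180 randomised per arm.

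- Two-sample formula without clustering: 142 per arm.
- 150 × 1.2 = 180, which reproduces the randomised number.
- Loss implied by 180 to 150: 30 per arm, 30/180 = 16.7%.
- A true 20% loss from 180: 180 × 0.20 = 36 per arm, leaving 144.

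So about 30 to 36 patients per arm would be missing from a complete-case analysis. The documents do not say how many of them would be lost before and how many after month 6. Patients who miss only month 6 would also leave the repeated measures ANOVA; their number is not given.

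**2. Is this a power problem?** Without clustering, power is 80.7% with 144 per arm, 82.3% with 150 and 88.5% with 180. Completer power stays above 80%, so the issue is who is analysed.

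**3. What each method uses.**

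| Method | Needs | Patient seen at month 6, lost by month 12 | Link to intention to treat |
|---|---|---|---|
| Repeated measures ANOVA | baseline, 6 and 12 months | dropped | one of the tests above the sentence |
| Multilevel analysis | at least one follow-up value | kept | one of the tests above the sentence |
| 12-month ANCOVA | baseline and 12 months | dropped | named after the sentence |

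**4. Possible bias of the ANCOVA.** The documents give no drop-out mechanism and no correlation between visits, so these are assumptions: no true effect, 180 per arm, SD 1.5, correlation 0.6 between all visits, 20% lost by month 12 in each arm, everyone seen at month 6, no clustering. Loss follows a logistic model in the standardised baseline-to-month-6 change, with poor responders more likely to leave.

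The bias is approximately the coefficient of month 6 in a regression of month 12 on baseline and month 6, multiplied by the difference between arms in the mean month-6 residual (given baseline) of the patients retained. With correlation 0.6 that coefficient is (0.6 − 0.6 × 0.6)/(1 − 0.6²) = 0.24/0.64 = 0.375. Simulation gives the apparent benefit:

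| Logit slope per SD | ANCOVA, mechanism in intervention arm only | ANCOVA, same mechanism in both arms | Likelihood estimate using month 6 |
|---|---|---|---|
| 0.5 | 0.04 | about 0 | 0.00 |
| 1.0 | 0.07 | about 0 | 0.00 |
| 1.5 | 0.09 to 0.10 | about 0 | 0.00 |

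In the one-arm case the false-positive rate of the ANCOVA is about 6%, 8% and 10 to 11%, against a nominal 5%. With the same mechanism in both arms it is 5 to 6%. Against the 0.5 target, the bias is 0.04/0.5 = 8% to 0.10/0.5 = 20%.

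The size depends on the correlation. If month 6 and month 12 correlate at 0.7, the coefficient is (0.7 − 0.36)/0.64 = 0.53, and at slope 1.5 the bias rises to about 0.093 × 0.53/0.375 = 0.13.

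**The case against.** The strongest reply is that the plan already contains the remedy. The sentence "Repeated measures analysis of variance and multilevel analysis for longitudinal data will be used to examine longitudinal differences between groups" places multilevel analysis beside repeated measures ANOVA for the primary outcome, and the intention-to-treat statement refers to both. A likelihood-based multilevel model keeps patients with partial follow-up. A reader might infer that the HbA1c result as such drops the expected 20%, or that the trial is a completer analysis throughout. The documents do not support that, because one of the three methods retains these patients and no hierarchy among the three is stated.

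Four further objections carry weight:

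- The intention-to-treat sentence comes before the ANCOVA, so the label attaches directly only to the first two methods. The ANCOVA matters because it is given the attributable 12-month effect.
- Missing data are addressed through sensitivity analyses, and an article may leave the imputation model and the analysis set to the full plan. This point does not rest on those details. It rests on the methods that the article itself names and the roles that it gives them.
- The bias requires a mechanism that differs between arms. Peer activities are only encouraged, and only in the intervention arm, so reasons for leaving could differ. But skipping an activity is not missing a blood test, and both arms have the same follow-up visits. The asymmetry is possible but not shown, and the likelihood estimate is unbiased in the simulation because loss was made to depend on observed values.
- A reader might also infer that repeated measures ANOVA loses much power because it averages in the baseline visit. That holds only for the between-group main effect. The article speaks of longitudinal differences and of change, which points to the group-by-time test. With 150 per arm, a 0.5 effect at both follow-ups, SD 1.5 and correlation 0.6, its power is about 92%, so low power is no argument here.

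**Conclusion.** The point holds in a limited form. Repeated measures ANOVA and the 12-month ANCOVA are complete-case as written, imputation is confined to sensitivity analyses, and only the multilevel model keeps partial follow-up. The intention-to-treat label therefore covers a method that drops patients with a missed visit, and the effect attributed to peer support ignores month-6 HbA1c that the trial collects.

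About 36 of 180 patients per arm are affected at a 20% loss, or 30 by the plan's own numbers. The resulting ANCOVA bias is roughly 0.04 to 0.10 HbA1c points if loss depends on month-6 response in one arm only, and about zero if the arms share the mechanism. These bias figures rest on an assumed visit correlation of 0.6, assumed drop-out slopes and no clustering; they show what could happen and are not a forecast. Because the correction is nearly free and uses a model already in the plan, it should be made.

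**What to change.** In Data analysis:

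1. Make the multilevel model already named there the intention-to-treat analysis of HbA1c. Use all observed month-6 and month-12 values as outcomes, baseline HbA1c as covariate, arm-by-visit terms and clustering by health centre. Take the 12-month effect from it.
2. Drop repeated measures ANOVA, or call it supportive.
3. If the 12-month ANCOVA is kept, run it on multiply imputed data with month-6 HbA1c in the imputation model.
4. State that patients with no follow-up HbA1c add nothing to the multilevel estimate, and cover them in the missing-data sensitivity analyses already planned.

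The cost is a change of wording and slightly more modelling; no further data are needed. The downside is reliance on missing at random, which the planned sensitivity analyses under other assumptions can probe.

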### Study design and setting

This study is a cluster randomised controlled trial implemented and reported in accordance with the requirements of the CONSORT statement [13] and its extension to cluster randomised trials [14]. The participants were randomly designated to either an intervention arm, which implements the usual care system and the peer support intervention, or a control arm which implements a usual care system, with geographical location being the unit of cluster randomisation.

All participants are patients with type 2 diabetes who receive primary health care at 12 rural community health centres located in Liu-he District, Nanjing, and Gao-gou Town, Huaian, in Jiang Su province. The study team coordinates and works hand-in-hand with the staff members at each community health centres to implement and monitor the study.

Figure 1 is a CONSORT diagram of the study design.

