#### Group allocation

Community health centres will be stratified by size and existing structure of primary diabetes care service. Allocation to intervention or control group is governed by a random number generation process using SAS 9.1 statistical software independently.

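### Adjustment for clustering is conditional and has no stated criterion, so the HbA1c comparison in this cluster randomised trial can exceed its 5% error rate

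*Protocol article*

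**What the plan says.** The protocol article describes a cluster randomised trial, "with geographical location being the unit of cluster randomisation" (Study design and setting), in patients who "receive primary health care at 12 rural community health centres". The same section commits to the CONSORT extension for cluster trials. Group allocation describes the unit as the centre: "Community health centres will be stratified by size and existing structure of primary diabetes care service". Sample size calculation speaks instead of randomisation groups of 8 to 15 people, which is the size range that the Intervention group section gives for peer groups.

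The primary outcome is HbA1c: "The primary expected outcome is the change in HbA1c at baseline compared to the sixth month and baseline to the twelfth month" (Outcome measures).

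Three statements in Data analysis bear on clustering:

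- Longitudinal comparison: "Repeated measures analysis of variance and multilevel analysis for longitudinal data will be used to examine longitudinal differences between groups". The levels of the multilevel analysis are not named.
- Clustering: "Evidence of clustering by clinic site and primary care provider will be examined and adjusted for analyses as needed". No test, threshold or other criterion follows.
- 12-month effect: analysis of covariance, spelled out as "linear regression models for 12-month measurements with baseline scores and intervention arm as covariates". No cluster term is listed.

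No other section requires the randomised unit to be in a between-arm analysis. The document gives no ICC and no design effect.

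**The concern.** When clusters are randomised, the cluster belongs in the analysis because of how allocation was done, not because correlation is visible in the data. The plan looks first and decides afterwards, and it does not say what would count as a need. With about 12 centres, a test for clustering has little power at ICCs that already matter, so a look-then-decide rule can often end in an analysis that treats patients as independent. In those cases the standard error of the arm difference may be too small, and a difference between centres may be read as an effect of peer support. The primary comparison and every secondary comparison are exposed. Because the criterion is open, the choice can also be made after the results are known.

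**Working it through.** **Inputs from the protocol article.** 12 centres; two-sided 5% significance; 80% power; difference 0.5 and SD 1.5; 180 randomised per arm; 20% drop-out.

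**Assumptions.** None of these is in the document:

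- The centre is the randomised unit, with six centres per arm of equal size. Completers per arm are 180 × 0.8 = 144, so m = 144/6 = 24 per centre.
- The ICC is 0.01 to 0.05.
- Three readings of *as needed* are tried: adjust if the F test of centres within arm gives p<0.05; adjust if it gives p<0.20; adjust whenever the estimated ICC is positive (F>1).

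**Plan's own figure.** The nominal error rate is 5%. With ICC 0, the unadjusted t test simulates at 5.0%, as it should.

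**Never adjusted, closed form.** The design effect is DE = 1 + (24 − 1) × ICC, and the true error is 2(1 − Φ(1.96/√DE)).

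- ICC 0.01: DE = 1.23, error 7.7%
- ICC 0.02: DE = 1.46, error 10.5%
- ICC 0.03: DE = 1.69, error 13.2%
- ICC 0.05: DE = 2.15, error 18.1%

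**Simulation.** 200,000 trials per ICC with no treatment effect. The unadjusted analysis is a t test on patients (286 df). The adjusted analysis is a t test on centre means (10 df). The rule picks one of them according to the trigger. Entries are percentages.

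| ICC | Clustering detected at 5% | Never adjusted | Adjust if p<0.05 | Adjust if p<0.20 | Adjust if estimated ICC > 0 | Always adjusted |
|---|---|---|---|---|---|---|
| 0 | 5.0 | 5.0 | 4.8 | 4.1 | 3.3 | 5.0 |
| 0.01 | 13.9 | 7.6 | 6.6 | 5.2 | 4.0 | 4.9 |
| 0.02 | 25.9 | 10.5 | 8.1 | 5.9 | 4.6 | 5.1 |
| 0.03 | 38.5 | 13.2 | 8.6 | 6.0 | 4.8 | 5.0 |
| 0.05 | 60.5 | 18.3 | 8.5 | 5.8 | 4.9 | 5.0 |

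**Interval width, always adjusted against never adjusted.** The ratio of average widths is about (2.228/1.968) × √DE × 0.975. The first factor is the ratio of t quantiles on 10 and 286 df. The factor 0.975 is the mean of an estimated SD on 10 df relative to the true SD.

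- ICC 0.01: 1.132 × 1.109 × 0.975 = 1.22 (simulated 1.23)
- ICC 0.05: 1.132 × 1.466 × 0.975 = 1.62 (simulated 1.63)

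**Power of the always-adjusted analysis.** SE = 1.5 × √(2 × DE/144), with 0.5/SE as the non-centrality of a t test on 10 df. Power is 63.4%, 56.1%, 50.2% and 41.5% at ICC 0.01, 0.02, 0.03 and 0.05. An analysis of 144 independent patients per arm would have 80%.

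**The case against.** The strongest reply is that the plan does not ignore clustering. It commits to examining it, it names clinic site as a level, and the sentence on longitudinal differences names multilevel analysis, which is the usual way to model centres. That sentence covers primary and secondary outcomes. Effectiveness is to be judged with the tests named up to that point, and the analysis of covariance comes later, so it is not clearly the primary test. This stands in part: an analysis that properly includes the centre is compatible with the text. But the multilevel analysis may mean only visits within patients, and if it already contained the randomised unit, a conditional sentence about adjustment would have no purpose.

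A second reply is that the size of the excess belongs to the assumed trigger. This also stands: the two more lenient triggers in the table remove most or all of the excess. The fault is the missing criterion, and inflation is possible rather than established.

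A third reply is that a condensed article leaves such matters to the analysis plan. That is true of degrees of freedom or covariance structure. Here the article states a rule, and an analysis plan that followed it would inherit the problem.

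Two stronger readings are tempting and are not supported. A reader might infer that the standard errors will be too small and that the error rate is up to 18%. That figure belongs to never adjusting, which the plan does not propose. A reader might also object that the peer-leader group is not among the levels named. If peer groups, formed by area of residence, lie within centres, an analysis at centre level already absorbs most of that correlation.

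**Conclusion.** The point holds as a fault in a stated rule. Adjustment for the randomised unit is optional, its criterion is open, and no other text makes it mandatory, so the HbA1c test can exceed 5%. On the assumptions shown, the error is about 7 to 9% if the trigger is a 5% F test and 5 to 6% with a p<0.20 trigger. There is no excess if adjustment follows any positive ICC estimate, and 8 to 18% is the worst case of no adjustment. Unconditional centre-level analysis holds 5% throughout.

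These sizes rest on an assumed ICC, equal centres and a 6:6 split. At ICC 0 there is no excess. The simulated outcome has no baseline covariate. Under the planned analysis of covariance the relevant ICC is the residual one, which the document does not give. If the unit randomised is not the centre, the numbers change but the argument does not.

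**What to change.** In Data analysis, delete *as needed*. State that every between-arm analysis, both the analysis of covariance and the longitudinal model, for primary and secondary outcomes, accounts for the unit actually randomised whatever the observed ICC. Either a random effect for that unit with a small-sample correction, or an analysis of baseline-adjusted cluster means, would serve. Report the ICC. Reconcile Study design and setting (location), Group allocation (health centre) and Sample size calculation (randomisation groups of 8 to 15) on what the unit is. A model with a peer-group random effect in the intervention arm only may be added as an optional sensitivity analysis.

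The change is to wording and needs no new patients, visits or data. Its price is precision: intervals about 23% wider at ICC 0.01 and 63% wider at 0.05 than an unadjusted analysis on these assumptions, with the lower power shown above. The unadjusted analysis does not avoid that loss when clustering is present; it leaves it out of the interval.

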#### Intervention group

Patients are divided into groups of 8–15 people and assigned to peer leaders for 12 months according to their area of residence. In addition to receiving the same training and follow-ups as the control group, patients from intervention groups were suggested and encouraged to take part in monthly group activities with peer leaders. If possible, casual activities (such as phone calls, WeChat voice messages, physical exercises, group member’s family visits, shopping together, etc.) are also recommended. The first meeting is an introductory discussion of group members’s backgrounds and their disease history, through which the leaders established understanding and relationship with the peers. In subsequent interactions, the leader and peers will discuss the following issues: their current and target values for HbA1c, blood lipids and blood pressure; self management skills such as using a glucose meter and appropriate strategies for hypoglycaemia; lifestyle changes around healthy diets, physical activities, foot care, and stress control. The subsequent monthly activities include interactions designed by the research team, peer leaders, as well as college student volunteers. Several cultural group activities will be organized such as Chinese hand calisthenics and body calisthenics, how to choose daily nutritional meals, knowledge competition, and singing songs that were integrated with health education topics. Group members also shared similar experiences on lifestyle, family life, personal hobbies and experiences to support each other in achieving goals. Peer leaders documented each encounter and recorded each time the date, number of participants, the nature of encounter, approximate duration of contact, and topics discussed. In addition, peer leader meeting will be held every six months. In the leader meetings, peer leaders will share their experiences and discussed the problems they confronted in their groups. The research team will aid them discover the solutions and provide them with further training when necessary.

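### Adjustment for clustering depends on a check by site and care provider, so dependence within the peer groups can drop out of the HbA1c standard error

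*Protocol article*

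**What the plan says.** All references are to the protocol article.

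- **Data analysis**, on clustering: "Evidence of clustering by clinic site and primary care provider will be examined", with adjustment to follow only where it is found necessary.
- **Data analysis**, on the 12-month effect: ANCOVA, spelled out as "linear regression models for 12-month measurements with baseline scores and intervention arm as covariates". No cluster term is listed.
- **Data analysis**, on the longitudinal comparison: "Repeated measures analysis of variance and multilevel analysis for longitudinal data will be used". The levels of the multilevel model are not given.
- **Intervention group**: "Patients are divided into groups of 8–15 people and assigned to peer leaders for 12 months according to their area of residence". The section on the control group describes no peer leader or peer group.
- **Study design and setting**: patients come from 12 health centres, "with geographical location being the unit of cluster randomisation".
- **Group allocation**: "Community health centres will be stratified by size and existing structure of primary diabetes care service".
- **Sample size calculation**: the same range of 8 to 15 appears as the size of a randomised group. No ICC or design effect is stated.

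**The concern.** Intervention patients spend a year in a small group under one leader, with monthly activities. Their HbA1c changes are likely to be correlated within the group, on top of any correlation within the randomised unit. The plan names two levels at which to look for clustering, and the peer group is not one of them. More importantly, even at the two named levels it adjusts only if the check suggests a need.

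A check across 12 centres has little power to detect dependence that sits in small groups in one arm. When it finds nothing, the ANCOVA as written treats patients as independent. The standard error of the primary HbA1c comparison is then too small and the chance of a false claim of benefit exceeds 5%.

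**Working it through.** **Inputs from the documents.** SD 1.5, difference 0.5, two-sided 5%, 80% power, 150 completers (read as per arm, since 150 × 1.2 = 180 and 180 is stated per arm), peer groups of 8 to 15, 12 centres.

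**Assumptions.** Peer-group ICC 0.01 to 0.10; control patients independent; no separate centre effect unless stated.

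**1. The plan's own figure.** Without clustering, n per arm = 2 × [1.5 × (1.960 + 0.842) / 0.5]² = 141.3, so 142. The stated 150 is slightly larger. If the surplus were a clustering allowance, 150/141.3 = 1.062 would imply an ICC of 0.062/7 = 0.009 for groups of 8 and 0.062/14 = 0.004 for groups of 15. The sample size therefore holds little or no reserve for clustering.

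**2. All clustering ignored.** With m patients per group, DE = 1 + (m − 1) × ICC in the intervention arm and 1 in the control arm.

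- SE used = 1.5 × √(2/150) = 0.173
- Correct SE = 1.5 × √((DE + 1)/150)
- Type I error = 2 × [1 − Φ(1.96 × SE used / correct SE)]

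| m | ICC | DE | Correct SE | Type I error | Power with correct SE |
|---|---|---|---|---|---|
| 8 | 0.01 | 1.07 | 0.176 | 5.4% | 81% |
| 8 | 0.05 | 1.35 | 0.188 | 7.1% | 76% |
| 11.5 | 0.05 | 1.525 | 0.195 | 8.1% | 73% |
| 15 | 0.10 | 2.40 | 0.226 | 13.3% | 60% |

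The power that 150 per arm would give without clustering is 82%.

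**3. The plan's conditional rule.** Simulation under the null, 40,000 trials per row: six centres per arm, 24 patients per centre, two groups of 12 in each intervention centre. The conditional rule is represented by a site F-test at 5%: centre-level analysis if significant, patient-level analysis otherwise.

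| Peer-group ICC | Clusters ignored | Screened by site | Centre always used | Screen significant |
|---|---|---|---|---|
| 0 | 5.0% | 4.8% | 5.0% | 5% |
| 0.02 | 6.2% | 5.7% | 4.9% | 9% |
| 0.05 | 8.3% | 7.0% | 5.1% | 16% |
| 0.10 | 11.7% | 8.4% | 5.3% | 31% |

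A second simulation (20,000 trials, 25 per centre, groups of 12 and 13) gave 7.3% and 8.8% after the screen for ICC 0.05 and 0.10, and 5.2% and 5.3% with centre always used.

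**4. Why centre-level analysis is enough for the type I error.** With total variance 1 and ICC 0.05, the variance of an intervention-centre mean is 0.05/2 + 0.95/24 = 0.0646. Under independence it is 1/24 = 0.0417. The ratio is 1.55, which equals 1 + 11 × 0.05. The spread of centre means already contains the peer-group component when groups lie inside centres.

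**5. Isolating the cause.** With no peer-group effect at all and a centre ICC of 0.02, the screened analysis still has a type I error of 8.0%, against 4.8% with centre always used. The conditional rule does harm whatever the source of the clustering.

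**The case against.** **Peer group as the cause.** A reader might infer that leaving out the peer group is by itself what makes the error bars too narrow. It is not: with centre always in the analysis and no peer-group term, both simulations stay near 5%. Nor do the documents support the idea that groups cross centres. Groups are formed by where patients live and randomisation is by location, which suggests nesting without stating it.

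**Size.** The 13.3% needs groups of 15, an ICC of 0.10 and no adjustment of any kind. The plan does include a site check, so the screened figures are closer to it, and at ICC 0.02 the excess is under one percentage point. A 5% F-test is only one reading of the rule. Two equal groups per centre is an assumption too; centres are stratified by size, so they differ. So is an independent control arm: control patients also attend interactive sessions, which could create some correlation there.

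**Detail for the analysis plan.** The exact random effects may be left to a statistical analysis plan, and the promised multilevel model could contain centre or peer group. This stands for the model's fine structure. It does not cover a stated rule that allows adjustment to be dropped, or an ANCOVA written out with no cluster term.

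**Peer group as randomised unit.** The Sample size calculation could be read as making the groups of 8 to 15 the randomised units. Leaving them out of the analysis would then be an outright error. The Study design and Group allocation sections place randomisation at location or health centre, so that reading is not established.

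**Conclusion.** The point holds as a defect of the conditional rule, with the unnamed peer group as a secondary gap. Followed as written, the plan can analyse patients as independent and leave peer-group dependence out of the HbA1c standard error. After a 5% site screen the type I error is about 5.7%, 7% or 8.5% for an assumed peer-group ICC of 0.02, 0.05 or 0.10. These figures rest on two groups per intervention centre, six centres per arm, groups nested in centres, no centre effect and an independent control arm. Naming the peer group while keeping the conditional rule would not cure the problem; always accounting for the randomised unit would, provided the groups are nested in it. The change should be made, but the inflation is moderate.

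**What to change.** 1. Replace the check-then-adjust sentence in Data analysis with a fixed rule: every between-arm analysis of HbA1c, including the 12-month ANCOVA, accounts for the randomised unit with small-sample degrees of freedom, whatever a significance test shows.
2. Reconcile Study design and setting, Group allocation and Sample size calculation on whether that unit is the centre, the geographical location or the group of 8 to 15.
3. Record a peer-group identifier for each intervention patient. Add peer group within centre as a random effect in the intervention arm, in the main model or, if that does not converge, as a sensitivity analysis. Report its variance, which shows how far results depend on the individual leader and so bears on the feasibility and sustainability objective.

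**Cost.** Analysis wording and one variable. The interval widens: by up to 1.30 times in the extreme row above (0.226/0.173), and, if 12 centres leave 12 − 2 = 10 degrees of freedom, by a further factor of 2.228/1.960 = 1.14. With few centres and groups the peer-group variance may be poorly estimated or the model may not converge.
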